#### Intervention modifications

The manipulations selected are gentle and safe for preschoolers. It is unlikely that pediatric *tuina* leads to severe adverse events. Any pain or discomfort, if any, during the intervention, are transient and will not bring to serious sequela. If participants withdraw during the treatment period, their reasons of withdrawal and adverse events will be recorded. They will be followed-up until the adverse events resolved.

#### Intervention adherence

For parents in both groups, a consultation will be available for clarification or helps during the treatment period through WeChat. We propose to use a combined approach that we will instruct the parents to perform the tuina intervention every other day and at least 3 times per week. Parents are required to record their massage practice on a logbook during the treatment period, and a researcher will remind them of carrying out the interventions two times a week. To encourage the subjects to complete the treatment, we will provide them with the intervention of the other group as a reward if they have completed the allocated treatment. During the whole process of intervention delivery and data collection, relevant information, international news, scientific research achievements, and other useful resources will be shared with the subjects, and those subjects who finish the whole process of the study will receive the resources 2 or 3 times a week until 6 months after the endpoint of the trial. A process evaluation will be carried out to better adjust the intervention acceptability and feasibility [41].

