### Blinding

Due to the nature of the intervention (pediatric *tuina*) and the active control intervention (parent-child interaction training), it is impossible to blind the practitioners and the subjects. Therefore, they will not be blinded. However, parents might have questions when filling the rating scales. If they have any problems, they can inquire to the research outcome assessors. For those outcome assessors who are in charge of guiding the parents to fill the questionnaires and collecting data, they will be blinded.

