#### Active control group: parent-child interaction training

Parents in this group will receive a parent-child interaction training program which includes progressive muscle relaxation exercise training for children and a health education booklet of ADHD and coping skills. The parents in this group will have to complete an online training session of progressive muscle relaxation exercise [39], which aims to help children reach a relaxation state by relaxing their muscles when facing stresses. The health education booklet covers the background knowledge of ADHD, suggestions, and examples of coping skills (e.g., coping skills for reaction to stress and conflict with children) and interaction skill training for parents (e.g., behavior management, self-regulation, improving organization, improving relationship, and use of encouragement) [40]. All the training contents are recommended by the Department of Health, the government of the Hong Kong Special Administrative Region. The training serves as an early intervention, with the emphasis on modifying the improper parenting methods and enhancing the positive parent-child interaction when the children are still at their preschool stage. Parents will be asked to complete an online written test after they have viewed the online training and teaching materials. They will be asked to spend at least 20 min every other day during the treatment period on doing progressive muscle relaxation exercises with their child and record their practice on a logbook (see Additional file 5).

During the study period, the children’s ongoing treatment, such as medications, behavioral therapies, and other services such as mental health service and parents-supporting activities will not be intervened in both groups. Information on their TAU will be recorded, and they will be asked not to start new treatment targeting ADHD symptoms during the study period. For subjects in both groups, they will be considered to have completed the program (completers) if they have attended the training lessons and performed the treatment at home for at least 3 days per week during the 8-week intervention period.

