#### Primary outcome measure

##### Swanson, Nolan, and Pelham parent rating scale (SNAP-IV-P)

The SNAP-IV Chinese Version ADHD Scale for parents is the primary outcome measure in this study. It has 26 items that include 18 ADHD symptoms (nine inattentive, nine hyperactive/impulsive) specified in the DSM-5. Items are rated for frequency by the parents on a 4-point scale (0 “not at all” to 3 “very much”) and average ratings per item are then calculated for each subscale. The Chinese version shows satisfying test-retest reliability (intraclass correlation = 0.59), internal consistency (*α* = 0.88), concurrent validity (Pearson correlations = 0.56), and discriminant validity [38].

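### Research news and other resources go to unblinded parents while those parents are still rating the outcomes, with no stated limit on content

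*Protocol article*

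**What the plan says.** Under Intervention adherence, the protocol article lists several ways to keep families engaged: WeChat consultation, reminders twice a week, the other arm's intervention as a reward for completing the allocated one, and a stream of information. On the last it says that "relevant information, international news, scientific research achievements, and other useful resources will be shared with the subjects". The timing is explicit: "During the whole process of intervention delivery and data collection". Completers keep receiving the material once the trial is over: "those subjects who finish the whole process of the study will receive the resources 2 or 3 times a week until 6 months", counted from the trial endpoint.

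On blinding, the article says "it is impossible to blind the practitioners and the subjects. Therefore, they will not be blinded". The people who are blinded are the "outcome assessors who are in charge of guiding the parents to fill the questionnaires and collecting data, they will be blinded".

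The primary outcome is scored by the parent: "Items are rated for frequency by the parents on a 4-point scale". The PAS and CSHQ are described as parent-completed, and the PSS asks parents about their own stress. Assessments are at baseline, week 4 and week 8 (Participant timelines).

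**The concern.** An unblinded parent as sole rater is unavoidable in this design, and the Discussion acknowledges the lack of blinding. What can be avoided is sending that rater research news between allocation and rating.

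Two features make a differential effect plausible. First, every parent must be willing to learn tuina to be enrolled (Inclusion criteria). An item favourable to tuina therefore reaches one group that is giving it and another that wanted it and was allocated to something else. Second, the field as the Background presents it leans favourable: it cites an acupressure trial that concluded in favour of acupressure over a stimulant drug, and a review suggesting that massage helps.

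Comparing preliminary effects is one of the four stated objectives. The Sample size section expects the confidence interval to inform later power analysis, and the same outcome measures are to be carried into the main trial. A reporting bias here would pass into that planning.

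**Working it through.** There is no figure in the plan to reproduce on this point. The check is whether the exposure, the rater and the rating times coincide, followed by how such a bias would act in the planned analyses.

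**Do they coincide?**

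| Element | What the article says | Section |
|---|---|---|
| When material is sent | throughout treatment and data collection | Intervention adherence |
| Who receives it | the subjects, with no distinction by arm | Intervention adherence |
| Content | research achievements, news, other resources; no limit stated | Intervention adherence |
| Who rates SNAP-IV-P, PAS, CSHQ, PSS | the parent | Outcome measures |
| Is the parent blinded? | no | Blinding |
| Post-baseline ratings | weeks 4 and 8 | Participant timelines |
| Stated protection | blinded assessors; practitioners kept out of assessment | Discussion |

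They coincide. The stated protection covers the people handling the forms, not the person whose judgement fills them in.

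**How a bias would act.** Let δ be the true between-arm difference, Δ the true change within an arm, and b(T) and b(C) the average shifts in ratings caused by the material in the tuina and control arms, signed so that positive means improvement.

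- Between arms (the mixed model): observed difference = δ + [b(T) − b(C)]. Equal shifts cancel; unequal shifts do not.
- Within an arm (the repeated-measures ANOVA in Statistical analysis): observed change = Δ + b. Nothing cancels here, even if b(T) = b(C).
- Both limits of a confidence interval move by the same bias, so reporting 95% intervals conveys sampling error and not this error.

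**Scale, under assumed biases.** The documents give no bias, so a range is shown. Inputs: 30 per arm (Sample size), or 22.5 per arm after the stated 25% dropout (30 × 0.75). Assumptions: normal approximation, standardised difference, no true effect.

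- SE = √(2/n). At n = 30 this is 0.258, with 95% half-width 1.96 × 0.258 = 0.51 SD. At n = 22.5 it is 0.298, with half-width 0.58 SD.
- Probability that the 95% interval excludes zero = Φ(b/SE − 1.96) + Φ(−b/SE − 1.96), where b is now the differential bias in SD.

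| Assumed differential bias (SD) | 30 per arm | 22.5 per arm |
|---|---|---|
| 0 | 5.0% | 5.0% |
| 0.1 | 6.7% | 6.3% |
| 0.2 | 12.1% | 10.3% |
| 0.3 | 21.3% | 17.2% |
| 0.5 | 49.1% | 38.9% |

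These rows show what a given bias would do. They do not estimate the bias in this trial.

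**The case against.** The strongest reply is that the article does not say what the resources contain. It does not say that they concern tuina or its efficacy, or that they differ by arm. Message content is a detail that a condensed article may leave to the full protocol. If both arms receive the same neutral items, the between-arm bias could be negligible. This stands as far as size and direction go. It does not remove the point, because the article itself fixes the timing and names research findings as part of the content. Identical material also cancels only if it is neutral about treatment.

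It can also be said that this is a feasibility pilot. Effects come last among its objectives, the analysis section calls the sample underpowered and urges caution, and the interval half-width of about 0.51 SD exceeds most of the biases tabulated. That lowers the stakes, but it is no reason to keep an error source that costs little to remove. Promised access to the other arm's intervention may also soften control-arm disappointment, at least for those who complete.

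A reader might further infer cross-arm contamination, with tuina content reaching controls or ADHD education reaching the tuina arm. The documents do not support this. Tuina delivery requires 5 hours of training, a passed skills assessment and an individual prescription, which a news item does not supply. Both arms are asked not to start new ADHD treatment, and the other arm's programme comes only after completion. The Discussion also says that both arms are meant to improve parents' knowledge of ADHD, so such knowledge in the tuina arm is intended.

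**Conclusion.** The plan sends research material with no stated content limit to unblinded parents before they complete the week-4 and week-8 scales, and no stated safeguard protects those ratings. This is an avoidable source of reporting bias in the preliminary between-arm effect, and in the within-group changes even if both arms are affected equally. The between-arm part depends on the material favouring tuina, or otherwise acting differently on the two arms; the article neither says so nor rules it out. It would therefore be too strong to state as fact that the trial feeds expectancy.

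The size is unknown. A reader might be tempted to put it in terms of the main trial: if a true difference of 0.3 SD were inflated to 0.5 SD, n per arm = 2(1.96 + 0.84)²/d² would give 63 instead of 175. The arithmetic is right, but the added 0.2 SD is invented, and the comparison supposes planning from the raw point estimate, whereas the Sample size section points to the lower limits of the interval. It is not evidence of how large the problem is. The case for a change rests on the exposure being avoidable and the remedy cheap.

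**What to change.** Amend Intervention adherence so that research findings and treatment-related resources are held back until the family's week-8 questionnaires have been received. The section already offers resources for 6 months after the endpoint, so they are delayed and not lost. Until then, send only reminders and schedule messages, or material that is neutral on treatment effects, identical in both arms, and logged with date and content.

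The cost is one minor engagement aid during the 8 weeks; the twice-weekly reminders and WeChat consultation remain. Study status says that recruitment is open, so families enrolled before and after the change would have slightly different adherence support. Adherence is itself a feasibility outcome, so the date of the change should be recorded and reported with it.

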## Outcome measures

### Feasibility outcomes

The study will assess the following feasibility outcomes throughout the 8-week study period: (1) recruitment rate; (2) consent rate; (3) adherence to the intervention; (4) completion of study assessments, and (5) adverse events. Participant satisfaction will be assessed by parent self-report questionnaire and focus group interviews in the process evaluation.

### Patient-centered outcomes

Patient-centered outcomes include the following primary outcomes and secondary outcomes, which will also be used in the future main trial.

#### Primary outcome measure

##### Swanson, Nolan, and Pelham parent rating scale (SNAP-IV-P)

The SNAP-IV Chinese Version ADHD Scale for parents is the primary outcome measure in this study. It has 26 items that include 18 ADHD symptoms (nine inattentive, nine hyperactive/impulsive) specified in the DSM-5. Items are rated for frequency by the parents on a 4-point scale (0 “not at all” to 3 “very much”) and average ratings per item are then calculated for each subscale. The Chinese version shows satisfying test-retest reliability (intraclass correlation = 0.59), internal consistency (*α* = 0.88), concurrent validity (Pearson correlations = 0.56), and discriminant validity [38].

#### Secondary outcome measures

##### Preschool anxiety scale (PAS)

The PAS is a 34-item parent-rated scale, which assesses anxiety symptoms in young children across six subscales: panic attack and agoraphobia, separation anxiety, physical injury fears, social phobia, obsessive-compulsive, generalized anxiety/overanxious disorder. The measure has sufficient evidence supporting construct validity, and the total score and subscales have great internal consistency (*α* = 0.72-0.92) [42]. Wang et al. evaluated the applicability of PAS in China and concluded that PAS had acceptable psychometric properties, and applicable to assess anxiety syndrome of preschoolers in China. Correlations between each item and its subscales ranged from 0.50 to 0.78. Cronbach’s alpha coefficient, the split-half reliability coefficient, and the test-retest coefficient of the scale were 0.87, 0.83, and 0.70 respectively [43].

##### Children’s sleep habits questionnaire (CSHQ)

The CSHQ is a retrospective, 33-item parent questionnaire that has been used in several studies to examine sleep behavior in young children. Previous studies suggested that the CSHQ’s structure needs to be adjusted to accommodate the preschool children in China, and should be used with great caution [44, 45]. A final 4-factor structure CSHQ was suggested that compromised 28 items, with bedtime behaviors (*α* = 0.59), sleep behaviors (*α* = 0.62), morning wakings (*α* = 0.69), and daytime sleepiness (*α* = 0.67). The four factors represented improvements to the psychometric quality of the CSHQ and the reliability of subscales was all acceptable. Therefore, according to the studies above, we will use the revised 28-item CSHQ for measuring the sleep quality of the children [45].

##### Parental stress scale (PSS)

The PSS is a measure of “individual differences in the level of stress associated with raising children,” which includes 18 items on the perception of parental stress and uses a Likert style rating scale [46]. The factor structure of the PSS was validated and manifested satisfactory internal consistency (*a* = 0.84). There was evidence of convergent validity with family functioning (*r* = −0.51), parental anxiety (*r* = 0.44), and depression (*r* = 0.35). Discriminant analyses showed low, non-statistical correlations with domains of children’s life quality (*r* = −0.07-−0.18) [47]. The Chinese version was validated by 257 Hong Kong Chinese parents with at least one child under 12 years, and the reliability was 0.89 [48].

## Process evaluation

Process evaluation is critical for interpreting and understanding the functioning of the intervention, which includes implementation, mechanisms, and context [49]. The parent-administered pediatric *tuina* therapy is a complex intervention. Parents will be trained in the hospital and perform the treatment on their children at home, and the *tuina-*prescriptions are individualized. These components highlight the requirements for investigating how implementation can be achieved across various contexts. Figure 4 shows a logic model we use to visually present the content of the intervention and its causal assumptions, the implementation, the contexts in which it is delivered, the potential impacts considered, as well as the outcomes it aims to achieve. A qualitative process evaluation embedded within the outcome evaluation will be performed to better understand the facilitators and barriers of the intervention functioning (Table 2).

**Fig. 4 Fig4:**
[figure not shown]
The parent-administered pediatric tuina logic model

**Table 2 Tab2:** Overall design of process evaluation

	Qualitative data		
	Self-report questionnaire	Focus group interview	Parents logbook
**Parents**	✓	✓	✓
**Practitioners**	✓		
**Research assistants**	✓		
**Outcome assessors**	✓		

### Data collection

Qualitative data will be collected through self-report questionnaires, focus group interviews, and parents’ written logs. A researcher will be in charge of the interviews. Parents will be informed of the qualitative process evaluation at the time of enrollment. Reflection from each interview and self-report will facilitate the subsequent data collection process.

#### Self-report questionnaire

The self-report questionnaires will gather information about the intervention delivery experience, facilitators, barriers, expectations, recommendations, and sustainability of the intervention. Parents will fill out the questionnaires in week 4 and week 8. TCM practitioners, research assistants, and outcome assessors will complete this assessment in week 8. Emphasis will be placed on the aspects of intervention delivery, feasibility, and acceptability.

#### Focus group interviews

Semi-structured interactive focus group interviews among parents will be conducted after the feasibility stage, providing them with the chance to articulate intervention delivery experience. This method will investigate parents’ perceptions of the intervention, and their opinions on what works or does not work about commencing the intervention. Questions will relate to the barriers and facilitators toward implementation, and what would be expected in the future to sustain and promote the intervention.

#### Parent logbooks

Parents’ logbooks will be used for supervising the performance of pediatric *tuina* delivery. Parents will be responsible for completing weekly logs online, specifying the acupoints locations, manipulations, duration, frequency, and their queries. An outcome assessor will review the logs and send reminders for the completion of logs where necessary.

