### Interventions

#### Intervention group: parent-administered pediatric tuina

Children in the intervention group will receive parent-administered pediatric tuina during the treatment period. Figure 3 presents the intervention implementation procedure. The parents will attend an online training program (2 training sessions, 5 h in total) to gain the knowledge and basic manipulations of pediatric *tuina* on ADHD symptoms in preschoolers. Contents of the training sessions will cover the manipulations and acupoints that are commonly used in treating ADHD. The instructor will, inspect their practice, and make feedback to them if there is any deviation. At the end of the training sessions, to assess the parents’ mastery of the contents and techniques, the parents will be asked to conduct the manipulations in the prescription (see Additional file 3) in front of the TCM practitioner via online video chat, or take a video of the manipulations in the prescription and submit it to the TCM practitioner for an assessment. Parents who have passed the assessment could the start conducting the intervention at home, while for those who have not passed, they will be asked to receive the training for one more time until they could appropriately conduct the manipulations. Then they will deliver the *tuina* on their child at home in the following 2 months according to the *tuina* prescriptions formulated by the TCM practitioner. The *tuina* prescriptions will comprise the acupoints selected, the corresponding manipulation, conduction frequency, times of each manipulation, and other necessary information. The parents will be told to deliver pediatric *tuina* therapy on their children every other day, with 20-30 min each day. A logbook will be used for recording (see Additional file 4). Videos of the manipulation techniques and relevant teaching materials will be provided to the parents via social media.

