We anticipate that there will be a few practical issues in performing this study. Firstly, the subjects will be provided with two consultations for TCM pattern identification (one at baseline and one at the end of first month) and the *tuina* prescription may be adjusted. However, the subjects may be more preferable to the original manipulation that they learned at the beginning as they have already mastered the manipulation and found benefit effects. In this case, we may offer them an option to continue the original manipulation. Secondly, parents usually have a great commitment to their family and their time schedule may be less flexible. Although we will inform them the schedule of the training lessons before baseline assessment, we foresee that some parents may not be able to attend all the lessons after randomization.

There are several limitations to this pilot study. First, given the nature of the intervention and the control intervention, it is impossible to blind either the parents, children, or TCM practitioners. To minimize the detection bias, the TCM practitioners would not be involved in the outcome assessment and the outcome assessors will be blinded during the process of intervention conduction and data collection. Second, although we will use MoCA to ensure that the parents have a normal cognitive function, the discrepancies in the learning abilities and education level may affect their mastery of the *tuina* technique and hence the effects of the treatment. However, it would truly reflect the implementation of the intervention in the daily clinical practice as the parents’ backgrounds usually vary. Finally, our control group did not test the *tuina’s* specific effect of exerting physical pressure on the specific body location based on meridian theory.

Our study will add to the current evidence of pediatric *tuina* for ADHD in preschool children based on meridian theory. Parent-administered pediatric *tuina* is a potential alternative therapy with fewer side effects and economic burden, and is more flexible for parents and children to receive the treatment. Our results will also inform the clinicians and practitioners about the feasibly of training the parents to administer the *tuina* technique to relieve their child’s ADHD symptoms.

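### An outcome assessor reviews weekly logs that reveal the tuina arm, which contradicts the stated blinding of outcome assessors

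*Protocol article*

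**What the plan says.** Three places in the protocol article bear on this.

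- **Blinding.** Practitioners and families cannot be blinded. The exception is the assessors: "For those outcome assessors who are in charge of guiding the parents to fill the questionnaires and collecting data, they will be blinded".
- **Discussion, limitations paragraph.** To keep detection bias to a minimum, TCM practitioners stay out of outcome assessment and "the outcome assessors will be blinded during the process of intervention conduction and data collection". This wording covers outcome assessors in general, and it covers the intervention period as well as data collection.
- **Process evaluation, Parent logbooks.** On log content: "Parents will be responsible for completing weekly logs online, specifying the acupoints locations, manipulations, duration, frequency, and their queries". On who reads the logs: "An outcome assessor will review the logs and send reminders for the completion of logs where necessary".

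The two arms keep different logbooks. Additional file 4 is cited for tuina and Additional file 5 for the relaxation exercise.

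SNAP-IV, the primary outcome, is rated by the parents. PAS and CSHQ are parent-completed, and PSS concerns the parent's own stress.

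**The concern.** A person who reads a family's tuina log cannot remain blind to that family's arm. If the same person then helps the parent with SNAP at week 4 or week 8, knowledge of the arm, and of the queries the parent has written in the log, could colour how questions are answered or how missing items are chased. The final report would also describe assessors as blinded when the trial's own procedure had unblinded at least one of them.

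This matters in a pilot because data collection procedures are among the things being tested (Objectives), and the same patient-centred outcomes are intended for the main trial. The Background criticises earlier massage trials partly for not blinding outcome assessors, and the Discussion presents this trial as overcoming the limitations of previous studies. A role conflict left in place could pass into the larger trial.

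**Working it through.** There is no figure in the plan to reproduce, and no power, variance or effect size is involved. The check compares the stated roles.

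**Step 1. Does the log reveal the arm?** The entries are described as "specifying the acupoints locations, manipulations, duration, frequency, and their queries". Acupoints and manipulations belong to tuina only; the control parents practise progressive muscle relaxation and record it in a separate logbook. If the reviewer sees both kinds of log, the content tells them apart. If the reviewer sees only tuina logs, receiving one identifies the tuina arm. Either way, the reader learns the allocation.

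**Step 2. When does the reader learn it?** Randomisation follows the baseline assessment, so baseline scores are unaffected. Logs are weekly through an 8-week treatment period, with outcomes at weeks 4 and 8. The knowledge therefore comes before both post-baseline assessments.

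**Step 3. Is the reader someone declared blinded?**

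| Section | Who is covered | Status |
|---|---|---|
| Blinding | assessors who guide parents and collect data | blinded |
| Discussion | outcome assessors, without restriction | blinded during intervention and data collection |
| Parent logbooks | an outcome assessor | reads logs that identify the tuina arm |

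The third row cannot stand with the second. It can stand with the first only if the log reviewer never guides parents or collects outcome data, and the article does not say so. Nor does it say that the logs are masked before review.

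**Step 4. How large is the exposure?** With 30 families in the tuina arm and 8 weekly logs each, the most that could be read is 30 × 8 = 240. This assumes full retention and every log submitted. It counts occasions for unblinding and gives no estimate of bias. The article states neither the number of assessors nor how they are assigned to families.

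**Step 5. What can assessor blinding protect?** The scales are rated by parents who know the arm and who, in the tuina arm, deliver the treatment. The Blinding section has assessors guiding completion, answering questions and collecting data. Blinding them can therefore limit prompting. It cannot remove detection bias from the ratings themselves.

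**The case against.** The strongest reply is that the roles may already be separate in practice. Parent logbooks refers to a single outcome assessor, and the Blinding section confines its statement to those who guide parents and collect data. A reviewer with no SNAP duties would be compatible with that section. This point stands as far as it goes: the documents do not show that the log reviewer also handles any given family's scales. It does not dispose of the contradiction, because the Discussion makes no such distinction and names the intervention period, which is when logs are reviewed. If separation is intended, the text has to say so.

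A second reply is that little is lost, since unblinded parents give the ratings, the article calls the trial open-label, and it lists unblinded parents as its first limitation. This also largely stands, and it keeps the expected effect small. The same fact is why assessor blinding should not be offered as a means of minimising detection bias.

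A third reply is that the main aim is feasibility and the effect comparison is described as underpowered and preliminary. That limits the stakes but leaves the text inconsistent.

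Some stronger readings are tempting, and the documents do not support them.

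- **That the trial's only safeguard against bias is gone.** The article also states sequentially numbered opaque envelopes, a coordinator blind to arms, a principal investigator outside post-baseline data collection, practitioners outside outcome assessment, and an active control.
- **That every SNAP assessment is handled by someone who knows the arm.** The assignment of assessors to families is not given.
- **That the assessors' own process questionnaire unblinds them.** The article says only that "TCM practitioners, research assistants, and outcome assessors will complete this assessment in week 8". A questionnaire about the assessor's own experience does not disclose a child's allocation.

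**Conclusion.** The concern holds in a limited form. The log-review duty contradicts the assessor blinding stated in the Discussion without qualification. It also contradicts the Blinding section unless the reviewer has no part in guiding parents or collecting outcomes. This is an error in what the article states, and not detail left to a fuller document.

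The size of any resulting bias cannot be derived from the documents. It is probably modest, on the assumption that assessors do no more than guide and collect, as the Blinding section describes. Recruitment, consent and completion of assessments are measured in ways this conflict does not touch. It should be fixed, because the claim is wrong as written and the correction is cheap, but it does not undermine the trial.

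**What to change.** 1. **Parent logbooks.** Assign log review and reminders to existing staff who have no role in guiding parents through the outcome scales or collecting them, and state that outcome assessors have no access to the logs. The researcher who sends the twice-weekly practice reminders (Intervention adherence) could do this only if that person is confirmed to have no outcome role; the article does not say.
2. **Discussion, limitations.** State that the outcome scales are reports by unblinded parents, so blinding the assessors only limits prompting. Do not present it as minimising detection bias.

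If a separate log reviewer is already in place, a sentence saying so, together with the bar on access, settles the first item. The cost is protocol wording and, at most, one task moved between existing staff, with no new visits, measurements or participants. Recruitment is described as open, so the change would still benefit families yet to enter.
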